## Abstract

**Background:** Radiation-induced dermatitis (RID) is a common complication of radiation therapy (RT). Although it has a high prevalence and can even trigger the premature end of conventional cancer therapies, there is no standard management. This study aims to evaluate whether topical use of Jaungo (Shiunko), a traditional herbal ointment mainly composed of *Lithospermi radix* and *Angelica sinensis*, could reduce RID compared to the water-in-oil type non-steroidal moisturizer in patients with breast cancer.

**Methods:** This is a prospective, single-blinded, randomized controlled pilot trial that investigates the effect of topical application of Jaungo for the prevention of RID in postoperative breast cancer patients scheduled for RT, in comparison with the non-steroidal moisturizer, with a random distribution of 50 patients across the two groups. RT will be administered for 5–7 weeks with a biological equivalent dose (BED_10_) of 60 Gy or more, and the interventions will be applied 3 times a day during RT duration. Participants will be assessed a total of nine times, including eight visits during the period of RT and one visit at a 2-week follow-up period after the end of treatment. The incidence and severity of RID, quality of life, skin reaction symptoms, and maximum pain related to RID will be measured. The incidence rate of grade 2 or higher RID using the Radiation Therapy Oncology Group (RTOG) in the two groups will be statistically compared as the primary outcome. The types and frequencies of adverse events will be also collected and evaluated. All assessments will be performed by independent radiology oncologists.

**Discussion:** This trial is currently ongoing and is recruiting. This study will determine the preventive efficacy of Jaungo in RID with postoperative breast cancer patients and provide evidence in traditional Korean medicine clinical practice.

## Introduction

Radiation-induced dermatitis (RID) is one of the most common complications of radiation therapy (RT) in patients with breast cancer (Bolderston et al., 2006), and it presents with a variety of symptoms such as pruritus, erythema, edema, desquamation, necrosis, ulceration, and hemorrhage. It has been reported that nearly 90% of patients undergoing RT for breast cancer develop erythema-symptomatic RID (Geara et al., 2018). RID can induce significant discomfort, including fibrosis and skin pigmentation, negative effects on quality of life, and may even delay or prematurely end conventional cancer therapies such as RT or chemotherapy (Iacovelli et al., 2020).

Although several interventions for preventing or reducing RID, including systemic oral medications, skin care practices, steroidal topical therapies, non-steroidal therapies, and dressings have been evaluated, there is no standard treatment that has clearly demonstrated its effectiveness (Chan et al., 2014). However, in the clinical setting, skincare practices such as gentle washing with soap, or applying a moisturizing cream are generally recommended for patients with RID, even though there is insufficient evidence supporting their efficacy (Wong et al., 2013; Chan et al., 2014).

A water-in-oil type non-steroidal moisturizer containing hyaluronic acid as the main component has shown potential as effective in preventing and minimizing RID in patients with breast cancer compared to an emollient base cream regarding the maximum severity of skin toxicity, burning, and desquamation (Primavera et al., 2006). It has been reported to act as a barrier to the irradiated area, as well as having wound regeneration and anti-inflammatory effects (Leonardi et al., 2008).

Jaungo (Shiunko in Chinese), a traditional herbal ointment mainly composed of *Lithospermi radix* and *Angelica sinensis*, has been commonly used to treat wounded skin caused by cuts, abrasion, frost, or burn (Huang et al., 2004). *Lithospermi radix* contains shikonin, acetylshikonin, and dimethylacrylshikonin, and *Angelica sinensis* contains ferulic acid and decursin as the major active components. These components have therapeutic effects on granulation tissue formation, speeding wound healing, reepithelization, and angiogenesis in addition to antibacterial and anti-inflammatory effects (Lu et al., 2008; Andújar et al., 2013; Ghaisas et al., 2014). Recent case series have reported that Jaungo showed favorable effects on radiation-induced scalp dermatitis in patients with brain tumors (Hayashi and Sato, 2011), and a previous clinical study showed that Jaungo reduced the incidence of RID in comparison with gentle washing with neutral pH soap with no safety issues in patients with breast cancer (Kong et al., 2016). However, the comparative clinical trial of Jaungo and the water-in-oil type non-steroidal moisturizer was not conducted.

Given the high prevalence and limited therapeutic options of RID, comparative studies between the topical agents which are recommended clinically to prevent RID in patients with breast cancer are needed. This is the first randomized controlled trial which aims to evaluate the preventive efficacy of adjuvant topical application of Jaungo for RID in breast cancer patients compared to the water-in-oil type non-steroidal moisturizer.

## Methods and Analysis

### Study Design

This is a single-center, prospective, single-blinded, pilot randomized controlled trial protocol, which aims to investigate the comparative efficacy of Jaungo (Hanpoong Pharm & Foods Corporation, Seoul, South Korea) and the water-in-oil type non-steroidal moisturizer (X-derm®, Pharmbio Korea Inc., Seoul, South Korea) at preventing RID in patients with breast cancer who underwent breast-conserving surgery. This protocol is based on the Standard Protocol Items: Recommendations for Interventional Trials (SPIRIT) (Chan et al., 2013). The SPIRIT flow diagram of the study is shown in Figure 1.

**FIGURE 1 F1:**
[figure not shown]
SPIRIT flow diagram of the study protocol.

### Ethics and Registration

The study was approved by the Institutional Research Board of Kyung Hee University Hospital at Gangdong, Seoul, South Korea (IRB number KHNMCOH-2020-12-001-002). This protocol has been registered on the Clinical Research Information Service (CRIS registration number KCT0005971), and the study will be conducted at the Kyung Hee University Hospital at Gangdong. We will fully inform the patients about the potential risks of this trial. Participants need to sign a written informed consent form to show that they understand the study program and are willing to enroll in the trial. They are free to choose whether to continue the trial at any time during the study.

### Sample Size

In this pilot study, the sample size was estimated according to the grade (Gr) of the Radiation Therapy Oncology Group (RTOG) (Cox et al., 1995) and National Cancer Institute (NCI) (Trotti et al., 2000) for the RID reported in the relevant literature. Kong et al. (Kong et al., 2016) investigated the incidence rate of RTOG Gr ≥ 2 in breast cancer patients with RID using Jaungo, which is the primary outcome in this study, at 46.7%. For non-steroidal moisturizer, there was no primary report using RTOG grade, but the incidence rate of NCI Gr ≥ 2 of RID in breast cancer patients was 9.0% (Leonardi et al., 2008). Clinically, the RTOG and NCI are common assessment grading tools, and each value of the incidence rate is compatible. Therefore, we estimated the incidence rates of the Jaungo and the moisturizer groups to be 0.467 and 0.09, respectively. The formula for calculating the sample size is as follows:$$n_{c}=\;\frac{\left(1+\lambda \right)\sigma^{2}{\left(Z_{\alpha /2}+Z_{\beta }\right)}^{2}}{\lambda d^{2}}$$

At the 5% significance level, considering an estimated withdrawal rate of 15%, a total of 50 participants, 25 in each group will be required to achieve 80% power.

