### Randomization and Blinding

Patients who have agreed to the trial will be screened on the day of screening (visit 0) whether they meet the inclusion/exclusion criteria. The enrolled participants will be randomly allocated to two parallel groups with a 1:1 ratio at the date of visit 1; either the Jaungo group or the moisturizer group. The random number will be generated by an independent statistician using a 2 × 2 randomized permuted block design. Each piece of paper with the allocation group information according to the random number will be sequentially inserted into an opaque envelope and sealed. After the screening, the enrolled participants will open the envelopes in order and will thus be assigned to either the Jaungo group or the moisturizer group.

Throughout the study process, the clinical research coordinator is responsible for recruiting participants, screening, and assigning random assignments. This trial is a single-blinded study because each intervention can be distinguished differently from the participants. The statisticians and envelope processors, group allocators, management pharmacists, and outcome assessors for the clinical trial are all independent. Additionally, the principal investigator and sub-investigator will be blinded to the assigned group.

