Jaungo, a traditional herbal ointment consisting of *Lithospermi radix* and *Angelica sinensis*, is standardized based on the Korean Pharmacopeia. It has been authorized as a topical drug for dermatitis by the Korea Food and Drug Safety Administration (KFDA). In clinical practice, Jaungo has been used to treat a variety of dermatopathy symptoms, including RID. A few clinical trials have demonstrated the preventive effects of Jaungo on RID. A recent study found that Jaungo reduced the incidence of Gr ≥ 2 (46.7 versus 78.6%) and Gr 3 RID (20.0 versus 50.0%) without adverse events compared to general supportive skincare including gentle washing with neutral pH soap instead of prophylactic lotions or moisturizers, although it was not statistically significant (Kong et al., 2016). Additionally, brain tumor patients who underwent RT showed significant prevention of scalp dermatitis after topical application of Jaungo (Hayashi and Sato, 2011). In particular, shikonin, acetylshikonin, ferulic acid, and decusin, the major components of *Lithospermia radix* and *Angelica sinensis*, have been reported to have wound healing, antibacterial and anti-inflammatory effects (Huang et al., 2004; Hsiao et al., 2012; Ghaisas et al., 2014).

Given this background, we evaluated the comparative efficacy of Jaungo and the non-steroidal moisturizer in the prevention of RID in postoperative breast cancer patients. To our knowledge, this study is the first randomized controlled trial comparing topical agents to investigate the prophylactic efficacy between Jaungo ointment and the water-in-oil type non-steroidal moisturizer, which is one of the major clinical topical managements of RID for breast cancer patients with RID. This study can be considered as a noteworthy study protocol for highly prevalent RID without standard treatment, despite the limitations that double-blindness cannot be achieved, a pilot study with a small sample size, and the evaluation of outcomes may be subjective, depending on the assessors.

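### At the protocol's own planning rates, the 80% power is for finding more grade 2+ dermatitis with Jaungo, the opposite of the stated aim

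*Protocol article*

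**What the plan says.** The Abstract (Background) sets a directional question: whether Jaungo "could reduce RID compared to the water-in-oil type non-steroidal moisturizer in patients with breast cancer". The Introduction likewise states the aim as preventive efficacy relative to the moisturizer. The primary outcome is the incidence of RTOG grade 2 or higher RID, so lower is better. The Discussion reads it that way when it presents "46.7 versus 78.6" (per cent, Jaungo against general skincare) as a reduction.

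The Sample Size section takes 46.7% for Jaungo from an earlier Jaungo study graded on RTOG. For the moisturizer it uses a different study on a different scale: "the incidence rate of NCI Gr ≥ 2 of RID in breast cancer patients was 9.0" (per cent). It declares the two scales compatible and concludes: "Therefore, we estimated the incidence rates of the Jaungo and the moisturizer groups to be 0.467 and 0.09, respectively". The printed formula uses the two-sided critical value and the squared difference. The result is that "a total of 50 participants, 25 in each group will be required to achieve 80% power", allowing for 15% withdrawal at the 5% level.

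The Statistical Analysis section compares the two incidences with a chi-squared test. The Abstract closes with a firm promise: "This study will determine the preventive efficacy of Jaungo in RID with postoperative breast cancer patients".

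**The concern.** The planning rates give Jaungo about five times the incidence of the moisturizer (0.467/0.09 = 5.2). Because the formula squares the difference, the sign drops out. The 80% is then printed without saying which direction it covers, and a reader will take it as power for the stated aim of a reduction. No section says that the trial was sized to detect an excess of RID with Jaungo, and none gives a non-inferiority or equivalence margin.

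At stake is what the trial can be expected to show. If the planning rates are right, the likely result is a significant finding against Jaungo. If the moisturizer rate is near 9% and Jaungo is as good or better, the likely result is a non-significant difference, from a trial whose Abstract says that it will determine preventive efficacy.

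**Working it through.** **Inputs.** From Sample Size: Jaungo 0.467, moisturizer 0.09, 5% level, two-sided critical value, 80% power, 15% withdrawal. From Randomization and Blinding: "randomly allocated to two parallel groups with a 1:1 ratio". From Statistical Analysis: chi-squared test, taken here as the uncorrected Pearson test.

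**1. Reproducing 50.** The standard two-proportion formula (pooled variance under the null, unpooled under the alternative), with mean rate (0.467 + 0.09)/2 = 0.2785, is

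n = [1.96·√(2·0.2785·0.7215) + 0.8416·√(0.467·0.533 + 0.09·0.91)]² / 0.377²

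= (1.2425 + 0.4841)² / 0.1421 = 20.97, so 21 per arm.

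Then 21/0.85 = 24.7, so 25 per arm and 50 in total. Approximate power at 21 per arm is 80.1%. The plan's figure reproduces from these inputs.

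A side note: the single-variance formula as printed gives 28 per arm after withdrawal with a pooled variance and 23 with the average of the two binomial variances. This does not affect the point.

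**2. Which direction the power lies in.** Exact binomial enumeration of the chi-squared test at 46.7% (Jaungo) and 9.0% (moisturizer):

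| Evaluable per arm | Significant, Jaungo worse | Significant, Jaungo better |
|---|---|---|
| 21 | 0.833 | 0.0000007 |
| 25 | 0.892 | 0.0000002 |

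**3. Ceiling on power for a benefit if the moisturizer rate is 9%.** The best case is no events with Jaungo. With 0 of n against k of n, the statistic is 2n·k/(2n − k), which must exceed 3.84.

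- n = 21: k = 3 gives 126/39 = 3.23 (not significant); k = 4 gives 168/38 = 4.42 (significant). The chance of at least 4 events in 21 at 9% is 11.4%.
- n = 25: k = 3 gives 150/47 = 3.19; k = 4 gives 200/46 = 4.35. The chance of at least 4 events in 25 at 9% is 18.3%.

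If Jaungo halves the rate to 4.5% (an illustrative assumption), power is 4.7% (21 per arm) or 6.6% (25 per arm).

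**4. Dependence on the 9%.** Keep Jaungo at 46.7% and raise the moisturizer rate. The 60% and 70% are illustrative; 78.6% is the general-skincare rate in the Discussion, borrowed for illustration.

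| Moisturizer rate | Power for Jaungo better, 21 per arm | 25 per arm |
|---|---|---|
| 60% | 13% | 18% |
| 70% | 33% | 43% |
| 78.6% | 59% | 69% |

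**5. Expected precision, 21 per arm.** The half-width of the 95% interval for the risk difference is 1.96·√[(p₁q₁ + p₂q₂)/21].

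- 46.7% against 9%: 1.96·√(0.3308/21) = 0.246, about ±25 points.
- 9% in both arms: 1.96·√(0.1638/21) = 0.173, about ±17 points.

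**The case against.** The strongest reply is that nothing is miscalculated. The formula and the test are two-sided, Study Design and the Discussion describe a neutral comparison of efficacy, and at the stated rates 80% power to detect a difference is true. The trial is also called a pilot throughout, and small sample size is listed as a limitation. All of this stands, and it is why the 80% should be qualified by direction and not struck out as false. It does not remove the conflict: the Abstract asks about a reduction, the Sample Size section makes an explicit power claim, and nothing connects that claim to detecting harm.

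Three stronger readings are tempting, and the protocol does not support them.

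- A reader might infer that the trial has almost no power for its aim in any circumstances. That holds only at the protocol's own moisturizer rate. The test is symmetric, and power for a benefit reaches 59% or 69% at the illustrative 78.6%. At such a rate, however, the stated derivation of 50 no longer applies.
- A reader might infer that the 37.7-point gap is largely a product of comparing different studies. The 78.6% comes from patients on general skincare and the 9.0% from patients using the moisturizer. The protocol gives no untreated rate for the second study, so baseline risks cannot be compared. What can be said is that the rates come from different studies and scales, and that their compatibility is asserted without support.
- A reader might infer that a null result will be presented as similarity. No section plans an equivalence claim.

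**Conclusion.** The point holds, conditional on the protocol's planning rates. The quoted 80% power applies to an excess of grade 2 or higher RID with Jaungo, and so does not support the stated aim of a reduction. At 46.7% against 9.0%, a significant result favouring Jaungo has a probability below one in a million. With a 9% moisturizer rate, power for a benefit is at most about 11% to 18%, whatever the Jaungo rate. These figures assume the uncorrected chi-squared test and between 21 and 25 evaluable patients per arm. If the true moisturizer rate is well above 9%, the ceiling no longer binds, but the sample size then lacks its stated justification. Either way, the power statement needs correcting.

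**What to change.** In Sample Size:

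- State that, at the assumed rates, the 80% power applies only to detecting more grade 2 or higher RID with Jaungo.
- State that 50 is a pilot size without adequate power for the reduction aim, and give the ceiling of about 11% (21 per arm) to 18% (25 per arm) at a 9% moisturizer rate.
- Give the expected precision of the risk difference with 21 per arm: about ±25 points at 46.7% against 9%, and about ±17 points at 9% in both arms.
- Describe the compatibility of the RTOG and NCI rates as an assumption, or support it.

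In Statistical Analysis, report the risk difference with a 95% confidence interval alongside the chi-squared test. The choice of interval method can be left to the analysis plan.

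In the Abstract, replace the promise to determine preventive efficacy with wording about estimating the difference to inform a definitive trial.

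The cost is wording. No extra patients are needed. The downside is that the stated power becomes less favourable.

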### Patients

#### Inclusion Criteria

1) Adult participants who are at least 19 years old or older; 2) subjects who were diagnosed with invasive breast cancer and recommended surgery for breast cancer; 3) subjects who received breast-conserving surgery; 4) subjects who were recommended to receive adjuvant RT after surgery; 5) Eastern Cooperative Oncology Group (ECOG) performance status (Oken et al., 1982) 1 or below; and 6) understanding of the study and willingness to provide signed consent to participate.

#### Exclusion Criteria

1) Cancer invasion to skin (T4 in eighth American Joint Committee on Cancer (AJCC) (Amin et al., 2017) TNM staging); 2) unhealed scar on the breast; 3) metastatic stage; 4) subjects who have a history of RT in the thoracic area for any reason; 5) soft tissue disease; 6) uncontrolled diabetes mellitus with an HbA1c value of 6.5% or greater; 7) subjects who are now or planned to be pregnant or breastfeeding during the study schedule; 8) subjects who are allergic to the medication; 9) Low compliance with any reason, including communication failure; and 10) abuse of alcohol or medication.

#### Prohibited Concomitant Medications

1) Intravenous antibiotics; 2) steroidal medication; 3) vasoprotective medication; 4) other treatments related to RID, except for the intervention, such as traditional Korean medicine (acupuncture, moxibustion, and herbal medicines), self-treatment (parse, vitamins, health-functioning foods, general medicines, and home remedies); 5) no other topical ointments or creams should be applied to the irradiated lesion, except for regular moisturizing lotion.

#### Drop-Out Criteria

Any patient who meets one of the following conditions will be dropped out from the trial. 1) The subjects or their families withdraw consent to participate in the trial; 2) a violation of the inclusion/exclusion criteria is found during the trial; 3) a significant adverse event appears in the subject and/or it is difficult to continue the trial due to an adverse reaction; 4) any violation of the study protocol; 5) the compliance level of the intervention (Jaungo or moisturizer) is less than 70%; 6) subjects who take medications, etc. that may affect the results of this study without confirmation from the attending physician; 7) any cases that the attending physician judge as inappropriate to the trial; 8) subjects who pregnant during the trial period; 9) subjects who fail to follow up during the trial period; 10) subjects who died during the trial period.

The methods used to contact the subject must be recorded in the supporting documents in the case of subjects who fail to follow up to prove that reasonable efforts were made to contact them. The patients who dropped-out due to significant adverse events could be provided with appropriate treatment for side effects. In these cases, the attending physician shall continuously evaluate the subjects until the adverse reactions are resolved or determined to be permanent.

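### The drop-out rule removes patients from the trial, not only from the product, for skin-related events, so later outcome readings can be lost

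*Protocol article*

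**What the plan says.** The Drop-Out Criteria open with one rule for ten conditions: "Any patient who meets one of the following conditions will be dropped out from the trial". Some conditions are true exits (consent withdrawn, lost to follow-up, death). Others concern the product or its use:

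- Item 3: "a significant adverse event appears in the subject and/or it is difficult to continue the trial due to an adverse reaction".
- Item 4: "any violation of the study protocol".
- Item 5: "the compliance level of the intervention (Jaungo or moisturizer) is less than 70" per cent.
- Item 6: medicines that may affect the results, taken "without confirmation from the attending physician".

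Two other sections feed into this list. Prohibited Concomitant Medications bans steroids, "other treatments related to RID, except for the intervention, such as traditional Korean medicine" and self-treatment, and any other topical on the irradiated area "except for regular moisturizing lotion". Contraindications of Intervention orders the application stopped for skin irritation, local rash or itching.

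On care after drop-out, the section says: "The patients who dropped-out due to significant adverse events could be provided with appropriate treatment for side effects". The attending physician then follows these patients until the reaction resolves or is judged permanent.

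Outcome Measurement grades RTOG at every visit, but takes CSSP, Skindex-29 and NRS only at the start of RT, at its end and 2 weeks later. Statistical Analysis uses an ITT set with three exclusions. Dropping out is not one of them.

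**The concern.** The article has no status for a patient who is off the product but still assessed. A patient who stops the ointment, or whose skin reaction is treated, may therefore leave the trial because of the condition that the trial measures. Such losses are related to outcome. They may also differ by arm, because Randomization and Blinding says that participants can tell the products apart.

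Two things are at stake. The secondary scores have only two post-baseline readings, both late, so a mid-course exit removes them entirely. The primary outcome depends on seeing a grade 2 reaction at some visit, so an exit at grade 0 or 1 removes the visits at which it might have been seen. The 15% withdrawal allowance protects the number of patients. It does not protect against bias from who is lost.

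**Working it through.** **1. What happens to each kind of patient if the text is followed**

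| Patient | Rule met | Readings lost |
|---|---|---|
| Stops for itching or rash at grade 0–1 and falls below 70% compliance | Item 5 (or item 3) | Later RTOG visits; both late CSSP, Skindex-29 and NRS readings |
| Treated for RID after reaching grade 2 | Possibly item 4, or item 3 if severe | Late CSSP, Skindex-29 and NRS; any later rise in maximum grade. The primary event is normally already recorded |
| Leaves for a significant adverse event | Item 3 | As above, depending on timing; only clinical evaluation continues |

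The ITT set keeps these patients in the denominator but cannot supply readings that were never taken.

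**2. The plan's own allowance**

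Inputs from Sample Size: rates 0.467 and 0.09, two-sided 5%, 80% power, 15% withdrawal. The mean rate is 0.2785 and the difference 0.377. The usual two-proportion formula with pooled null variance gives

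n = [1.960 × √(2 × 0.2785 × 0.7215) + 0.842 × √(0.467 × 0.533 + 0.09 × 0.91)]² / 0.377² = 20.97, so 21 per arm.

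21 / 0.85 = 24.7, so 25 per arm, as stated. The plan thus allows for about 4 losses per arm (0.15 × 25 = 3.75).

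**3. When a product stop breaches 70%**

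Assumptions, since the article does not define compliance: the denominator is all planned applications (3 a day, every day of the course), use is perfect until the stop, and the stop is permanent.

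- 5 weeks: 35 × 3 = 105 planned. Below 70% needs 32 missed (73/105 = 69.5%; 74/105 = 70.5%). At 3 a day that takes 11 days.
- 7 weeks: 49 × 3 = 147 planned. Below 70% needs 45 missed (102/147 = 69.4%; 103/147 = 70.1%). That takes 15 days.

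A stop after day 24 of 5 weeks crosses the line on day 24 + 11 = 35. A stop after day 34 of 7 weeks crosses on day 34 + 15 = 49. Both are the last day of the course, when the end-of-RT reading is due. Only clearly earlier stops cost that reading: a stop after day 14 crosses on day 25 of 35, or day 29 of 49.

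**4. Scale for a late secondary score (illustration only)**

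Suppose no true difference, 25 per arm, and one arm loses its k worst scorers while the other loses none. Ignoring ties, the chance that a retained patient in that arm scores worse than a patient in the other arm is (26 − k)/52, against 0.50 without loss. For k = 4 this is 22/52 = 0.423. The null standard error with 21 and 25 patients is √(47 / (12 × 21 × 25)) = 0.086, so the shift is 0.077 / 0.086 = 0.9 SE.

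Simulation (20,000 sets) for other patterns:

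| Lost, arm A v arm B | Exit depends on score | Chance A worse | Shift |
|---|---|---|---|
| 4 v 0 | correlation 0.5 | 0.46 | about 0.4 SE |
| 2 v 1 | fully | 0.48 | 0.2 SE |
| 2 v 1 | correlation 0.5 | 0.49 | 0.1 SE |
| 0 v 2 | fully | 0.54 | 0.4 SE, opposite sign |
| 4 v 4 | fully | 0.50 | none |

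**5. Scale for the primary outcome**

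If a patient dropped before grade 2 were counted as having no event (an assumption), each later grade 2 reaction left unseen would lower that arm's observed rate by 1/25 = 4 percentage points.

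**The case against.** The strongest replies are these.

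- **Treatment of RID need not mean removal.** Item 6 covers only medicines taken without the physician's confirmation, which suggests that confirmed ones are tolerated. The examples in the ban on other RID treatments are traditional Korean medicine and self-treatment. This stands in part: the text is ambiguous. A reader might infer that any treated patient must leave, and the document does not establish that. But the bans on steroids and other topicals carry no exception for confirmed use, and item 4 covers any violation, so the site cannot tell which rule governs.

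- **The stop rule concerns product intolerance.** It sits among contraindications, beside hypersensitivity, and does not say the stop is permanent. With erythema in nearly 90% of irradiated patients, it cannot sensibly mean that every RID symptom ends use. This largely stands. What remains is that itching is also an RID symptom (Introduction), so the two may be hard to tell apart, and that an intolerant patient is dropped as well.

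- **Assessment may continue anyway.** Outcome Measurement makes no exception for drop-outs, and a condensed article may omit the detail. But the article states a rule, exit from the trial, in a list that also holds death and loss to follow-up. The one form of continued observation it names is clinical. If the full protocol already keeps these patients under assessment, only the wording needs aligning.

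- **Safety.** A reader might infer that patients are denied care. The text does not support that, since treatment and follow-up are provided for adverse-event drop-outs.

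**Conclusion.** The point holds as a minor design weakness. Followed as written, the rule ends trial participation for product-related events that can stem from the skin reaction, and provides for no further outcome scoring.

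The loss falls chiefly on CSSP, Skindex-29, NRS and maximum grade. The primary outcome is not immune: patients treated after grade 2 are normally already counted, but those dropped before grade 2 are not. Two stronger inferences fail, namely that the primary outcome is biased in a known direction and that drop-outs are excluded from the analysis. Nothing in the article shows which arm would lose more, and the ITT set retains drop-outs.

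The article gives no figure for how many patients would leave this way, so neither size nor direction can be estimated. The bias is zero if losses balance in number and kind. The extreme one-sided case reaches 0.9 SE on a rank comparison; the milder ones reach 0.1 to 0.2 SE. The compliance timings rest on the assumed denominator. If only applications due while use is permitted were counted, an instructed stop would never breach 70%.

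**What to change.** Amend the Drop-Out Criteria so that low compliance, a product stop under Contraindications of Intervention or for an adverse reaction, and physician-directed treatment of RID end use of the product where needed but do not end trial follow-up. For these patients:

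- continue the scheduled blinded RTOG assessments and the CSSP, Skindex-29 and NRS readings to the 2-week visit, unless consent is withdrawn;
- analyse them in their randomised arm;
- report product stops and RID treatment, with start dates, by arm.

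The decision to treat should stay with clinical judgement; no grade threshold is needed. The Adverse Events section already records event dates and treatment taken, so the addition is a short amendment and about one case report form entry. It needs no new visit, no extra staff and no change to the 50 patients.

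There are two downsides. Late scores will include the effect of any other treatment. And because the trial is already recruiting, patients dropped before the amendment remain under the old rule, so the date of the change should be reported.
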